### Objectives {7}

The primary objective of this study is to comprehensively assess and compare the effectiveness of three distinct BLT approaches for the treatment of depressive symptoms: (1) standard home-based BLT (*Light@Home)*, (2) BLT at the *LightCafé (LightCafé)*, and (3) BLT at the *LightCafé* with personalized timing of light and darkness using BBG (*LightCafé* +).

Secondary objectives are:i.The identification of predictors of treatment response, encompassing baseline clinical characteristics, sleep metrics, circadian parameters, and light-related behaviors.ii.Elucidation of underlying mechanisms of BLT’s efficacy by investigating the contribution of circadian rhythm changes, enhancing our understanding of the complex interactions between mood, energy levels, and sleep within the context of BLT and exploration of the neural effects of BLT by studying both functional and structural brain changes before and after treatment.

Importantly, we are not testing BLT’s efficacy for specific diagnostic categories; rather, we ask whether embedding BLT within a rich psychosocial setting and personalizing its timing can amplify and prolong its antidepressant effect, all while unraveling who benefits most and through which pathways. By moving from “Does BLT work?” to “How can we make it work better, for whom, and why?”, this multicenter RCT will lay the groundwork for personalized and embedded BLT protocols and real-world clinical guidelines.

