### Eligibility criteria {10}

#### General eligibility criteria

Eligibility will be assessed during the intake by study team members trained in administering the MINI International Neuropsychiatric Interview 5.0.0 (M.I.N.I.; [69]). The inclusion criteria are as follows:Age between 18 and 65.Diagnosis of unipolar or bipolar depression (seasonal or non-seasonal) confirmed by the M.I.N.I. [69].Currently experiencing a depressive episode, as indicated by a Quick Inventory of Depressive Symptomatology Self-Report (QIDS-SR; [70]) score of 6 or higher.Proficiency in either Dutch or English is required for questionnaire completion.

Participants are excluded from participation if they:Are currently experiencing a (hypo)manic or mixed episode, as determined by the M.I.N.I. assessment [69].Are presently in a psychotic episode, as determined by the M.I.N.I. assessment [69].Exhibit significant active suicidality, indicated by a score of 10 or higher on the M.I.N.I. module [69].Initiated antidepressant therapy (including medication, psychotherapy, BLT, or other specific depression treatments) within the last 2 months prior to study enrolment.Have a bipolar disorder but are currently not under mood-stabilizing treatment for at least 1 month at the recommended dosage.Have used melatonin or agomelatine in the past month.Are currently using antibiotics.Are currently taking medications that increase light sensitivity.Have travelled across more than one time zone in the past month or during the treatment period.Have travelled to sunny holiday destinations or engaged in outdoor winter sports in the past month.Have pre-existing eye and skin disorders such as retinitis pigmentosa, porphyria, chronic actinic dermatitis, and sun-induced urticaria.Have systemic disorders with potential retinal involvement, such as rheumatoid arthritis and systemic lupus erythematosus.Have color blindness (based on self-report).Worked night shifts within the last three months.Suffer from (retinal) blindness, severe cataracts, or glaucoma.Experience light-induced migraine or epilepsy.Are currently pregnant or have a child Younger than 18 months old.

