### Recruitment {15}

We intend to include participants year-round for approximately 2 years. The distribution of the recruitment burden is shared between two mental health clinics: GGzE’s aim is to include 171 participants, while LUBEC aims for 60. At GGzE, all individuals referred for BLT are approached for potential participation. Previous light therapy studies conducted at this center with the same enrolment strategy have achieved inclusion rates of approximately 100 participants per year. Given that this study is considered more extensive than previous research, we anticipate it will take approximately 2 years to reach the targeted enrolment of 171 participants. At LUBEC, BLT is offered for the first time, and only in conjunction with study participation. Recruitment efforts involve the collaboration with primary care and secondary mental health institutions for the referral of patients.

The rate of participant accrual is reviewed every half year. The number of participants who consented but did not qualify and the number of qualified, enrolled participants who dropped out will also be examined to detect patterns of insufficient recruitment rates. These will be addressed with modified recruitment strategies so that we can meet our recruitment goals.

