## Assignment of interventions: allocation

### Sequence generation {16a}

Eligible participants are randomized using block randomization via the Research Manager data platform [94]. To ensure a balanced distribution among treatment groups and minimize potential biases, participants are stratified based on several key factors, including chronotype (categorized as early, intermediate, or late based on the MEQ [86], clinical diagnosis (differentiating between unipolar and bipolar conditions according to the M.I.N.I. assessment), and participation in the melatonin assessment (indicated as either yes or no).

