### Primary Study Outcome – Clinical Improvement between Treatment Conditions

To compare the three different BLT administration strategies in terms of clinical improvement (measured as the difference in MADRS scores between baseline and post-treatment assessments), we will employ a multilevel mixed-effects modelling approach. MADRS scores will serve as the dependent variable, with a fixed effects for timepoint (*pre- and post-treatment*), and the interaction between timepoint and treatment arm (*Light@Home, LightCafé*, and* LightCafé* +). Random intercepts for participants and study centers will be included to account for individual differences and center-level variability, but only if they improve model fit, as determined by evaluation of the Akaike Information Criterion (AIC) and Bayesian Information Criterion (BIC). Random slopes for time within participants will also be considered and included based on the same criteria. Socio-demographic (age, sex) will be evaluated for potential confounding effects, similar to the credibility and expectancy of the treatment arms as assessed with the CEQ. The primary analysis will focus on the interaction between timepoint and treatment arm to determine whether clinical improvement differs across the three BLT strategies. Furthermore, multilevel logistic regression will be used to test differences in response (yes/no) and remission (yes/no) between treatment arms using the same structure and procedure as above.

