#### Identification of predictors of response and remission

Another aim of the study is to identify combinations of patient characteristics and behaviors that predict treatment response and remission. To achieve this, we will conduct AIC penalized bootstrapped stepwise logistic regression in both forward and backward directions, examining predictors of remission and treatment response in two separate models. The examined predictors will include:Demographic Factors: *Age, Sex, Educational Level*Clinical Characteristics: *Clinical Diagnosis, Severity of Depressive Symptoms, Diurnal Variation in Affect*Sleep-Related Factors: *Subjective Sleep Quality, Sleep Efficiency, Sleep Duration, Sleep Onset Latency, Midsleep Timing, Wake after Sleep Onset, Severity of Insomnia Symptoms, Energy Levels*Circadian Factors: *Circadian Phase, Intradaily Stability, Intradaily Variability, Phase Angle Difference between DLMO and Sleep Onset, chronotype.*Light-related parameters: *Light Sensitivity*Expectations: *Expectations of Treatment*

All predictors will be measured either at intake or during the baseline week. Prior to the stepwise regression analysis, we will assess multicollinearity by calculating the Pearson correlation coefficient and Variance Inflation Factor (VIF). Variables exhibiting a Pearson correlation coefficient greater than 0.8 or a VIF score exceeding 10 will be removed to mitigate multicollinearity and examined separately. A final competitive regression model will be run with all significant predictors.

To ensure the robustness of our models, we will run 1000 bootstrap samples and retain predictors that are significant in at least 60% of the bootstrapped samples. We will also calculate partial R-squared values for all predictors in the regression models to quantify the proportion of variance in the dependent variable explained by each specific independent variable while controlling for the influence of others. Finally, we will conduct variance partitioning to investigate the unique and shared variance explained by the predictors. By comparing the explained variance from regression models of individual predictors against those with combinations of predictors, we will compute both unique and shared variance. The vegan package in R will be used for variance partitioning, and results will be visualized using Euler plots from the Euler package.

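### The response-predictor models pool three light-therapy strategies without an arm term, and no model accounts for season of treatment

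*Protocol article*

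**What the plan says.** The Objectives {7} set a patient-selection question beside the comparison of strategies: "all while unraveling who benefits most and through which pathways". The section on identifying predictors states its own aim, to "identify combinations of patient characteristics and behaviors that predict treatment response and remission". It does so with one bootstrapped stepwise logistic model for remission and one for response. The candidates come in demographic, clinical, sleep, circadian, light and expectation blocks, 21 in all (3 + 3 + 8 + 5 + 1 + 1). The clinical block is "Clinical Diagnosis, Severity of Depressive Symptoms, Diurnal Variation in Affect". On timing, "All predictors will be measured either at intake or during the baseline week".

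On season, Recruitment {15} says "We intend to include participants year-round for approximately 2 years", and the eligibility criteria admit "Diagnosis of unipolar or bipolar depression (seasonal or non-seasonal) confirmed by the M.I.N.I". Sequence generation {16a} stratifies on chronotype, melatonin participation and clinical diagnosis, the last "differentiating between unipolar and bipolar conditions according to the M.I.N.I. assessment". For the primary MADRS model, "Socio-demographic (age, sex) will be evaluated for potential confounding effects", along with treatment credibility and expectancy. The QIDS-SR model adds clinical diagnosis and treatment duration. Season, start date and day length appear in none of these.

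Two other places relate patient characteristics to arm. The section on circadian effects tests whether baseline severity or sleep quality interacts with condition, and Methods for additional analyses {20b} explores strategy effects across diagnoses.

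**The concern.** The three arms differ in setting, coaching, timing of light and use of blue-blocking glasses. A model that pools them without an arm term estimates how a characteristic relates to outcome on average over the three. A characteristic that matters under one strategy only is diluted, and one whose effect reverses between strategies can vanish. A reader who takes the results as an answer to the selection question in the Objectives would read prognosis as strategy-specific benefit.

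Season raises a separate issue. If outcome depends on when in the year a patient is treated, and a baseline variable such as midsleep, energy or circadian phase also differs by time of year, the model may select that variable as a predictor of response although it only marks the calendar. The Objectives promise light-related behaviours as predictors, but the candidate list holds only light sensitivity, so measured baseline light exposure cannot absorb season either.

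**Working it through.** The documents give no sample size or power for the predictor models, so there is no stated figure to reproduce. The only trial input is N = 210, from Sample size {14}. Every effect size below is an assumption.

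**1. Dilution by pooling.** With equal arms and an effect in one arm only, the pooled log-odds is roughly one third of that arm's log-odds.
- Odds ratio 3: exp(ln 3 / 3) = exp(0.366) = 1.44.
- Odds ratio 2: exp(ln 2 / 3) = exp(0.231) = 1.26.
- Direct check for a binary trait, with 40% response wherever the trait has no effect: in the affected arm, odds are 3 × 0.4/0.6 = 2, so response is 0.667. The average over arms with the trait is (0.4 + 0.4 + 0.667)/3 = 0.489, odds 0.957. Without the trait, odds are 0.667. Ratio 0.957/0.667 = 1.43.
- Simulated at N = 210 with 45% response, binary trait: the pooled odds ratio is 1.45 and significant in 23% of trials (odds ratio 3), or 1.26 and significant in 12% (odds ratio 2). The trait-by-arm test has only about 16–36% power in these cases.
- Extreme case, log-odds slopes of +0.7, 0 and −0.7 in the three arms, 1,000 runs: the model without arm gives a mean slope of about 0.005 and flags the predictor in 3.6% of trials; the interaction test flags it in 94.7%.

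**2. Season proxy.** A baseline variable with no effect of its own differs between two seasons by 0.3 to 1.2 SD. Half the patients are treated in each season, about 40% remit, N = 210, with 1,000 runs per cell. Share of trials in which the variable is significant at 0.05:

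| Assumed season odds ratio | Season omitted | Season included |
|---|---|---|
| 1 | 4–6% | 3–5% |
| 1.5 | 5–11% | 4–5% |
| 2 | 7–23% | about 5% |
| 3 | 7–48% | 5–6% |

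These are single-predictor fits. They show the mechanism and do not simulate the planned stepwise selection or its 60% bootstrap rule.

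**3. Arm contrasts.** Allocation is randomised in permuted blocks of six (Concealment mechanism {16b}), so start date is unrelated to arm apart from chance. A covariate explaining a share R² of the outcome variance is worth a factor 1/(1 − R²) in sample size: 1/0.95 = 1.05 and 1/0.90 = 1.11. The R² values of 5% and 10% are illustrative; the documents give none.

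**4. Timing of predictors.** Randomisation protects characteristics measured before allocation from confounding by arm. Patients are randomised at the end of intake, however, and the expectancy questionnaire follows at B1 (Baseline phase; Table 1) in participants who are not blinded. Expectation of treatment, a listed candidate, can therefore partly carry allocation when arm is left out.

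**The case against.** The strongest reply is that these models do what their section promises. It speaks of patient characteristics that predict response and remission; arm is not a patient characteristic, and strategy-by-patient questions are placed elsewhere. That stands. A reader might infer that the whole plan cannot show who benefits from which strategy, but the moderation analyses and the diagnosis subgroups rule that out. What remains is that they cover three characteristics, none of them sleep timing or chronotype.

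It is also fair to say that the candidate list is worded as what the predictors will include, that the article calls its analysis plan an initial framework, and that forced covariates are often left to an analysis plan. Against that, this section already fixes the candidates, the collinearity cut-offs, the number of bootstrap samples and the retention rule, so the missing terms are worth naming.

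Four further inferences are tempting and not supported:
- That the models will pick up season. The documents show neither a season effect on response nor seasonal variation in any predictor. The efficacy review's larger effects in seasonal depression (0.60–1.08, against about 0.4 in non-seasonal depression) come from separate meta-analyses and concern diagnosis, not month of treatment.
- That season biases the arm comparison. It shifts all three arms alike.
- That seasonal pattern is dropped. The unipolar/bipolar split defines a randomisation stratum; the predictor called clinical diagnosis is not defined that way, and Trial design {8} names seasonal affective disorder separately. Its coding is simply left open.
- That chronotype sets the timing in LightCafé+. The section on personalised chronotherapeutic strategies sets it from current against target sleep onset.

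Finally, with 21 candidates, and melatonin-based ones available in only 72 participants, extra forced terms add to a real overfitting problem.

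**Conclusion.** The concern holds in a limited form. The predictor models can deliver general prognostic factors averaged over three strategies and nothing arm-specific, and season of treatment enters no model in the article. The dilution in step 1 follows from pooling equal arms, but its size depends on the assumed one-arm effect. Misattribution to season is possible and depends on two unknowns: the effect of season on response and the seasonal difference in the predictor. It is negligible if either is small. For the randomised MADRS and QIDS-SR contrasts the only gain is precision, of unknown size. This is a cheap improvement to make before analysis; it does not threaten the primary result.

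**What to change.** In the predictor section:
- Force treatment arm and day length at treatment start into both models, outside the stepwise selection.
- Code clinical diagnosis so that seasonal pattern is kept.
- Describe the remaining pooled predictors as prognostic, and say that they do not show who benefits from which strategy.
- Pre-specify one exploratory predictor-by-arm interaction on MADRS change, reported as an estimate with its interval. Baseline sleep timing (sleep onset or midsleep) is closest to the LightCafé+ timing rule and can be taken from actigraphy in all arms. The chronotype stratum is the alternative and has the advantage of being recorded at intake, before allocation.

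In the MADRS and QIDS-SR models, add seasonal pattern and day length at start as baseline covariates, each with its interaction with time, for precision.

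No new data are needed: start dates are known and seasonal status belongs to the entry diagnosis. The cost in each predictor model is two degrees of freedom for arm, one for day length and about one for seasonal pattern, in models that already have many candidates. The interaction will have low power unless effects differ strongly between arms, so a non-significant result should not be read as showing no difference.

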### Predicting treatment response

The next step in optimization involves more precise therapy selection upfront, as without knowing who benefits most, we risk offering intensive BLT protocols to unlikely responders. However, to date, we lack hypothesis‐driven investigations into which patient characteristics and behaviors predict BLT response. Secondary analyses in SAD cohorts suggest that individuals presenting with atypical features—such as increased appetite, hypersomnia, and a positive diurnal mood variation—alongside higher baseline BMI tend to experience the most rapid and robust improvement with morning light exposure [26, 27]. Those exhibiting melancholic symptoms—psychomotor retardation, early and late insomnia, appetite loss, pervasive guilt, and worse mood upon awakening—often derive little benefit [26]. Similarly, in treatment-resistant inpatients undergoing combined wake and light therapy, early diurnal symptom shifts, evening chronotype, and higher educational history have been linked to both short- and long-term remission [28]. Yet it remains unknown whether these results generalize across the full spectrum of unipolar and bipolar depressions. Clarifying these predictors is crucial: it would empower clinicians to stratify patients by likelihood of response, and ultimately render BLT a more efficient, cost-effective, and patient-centered antidepressant strategy.

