The following questionnaires and rating scales will be used during the study:**Mini-International Neuropsychiatric Interview (M.I.N.I.) PLUS 5.0** [69]: The M.I.N.I. is a brief, structured diagnostic interview designed to generate DSM-5 psychiatric diagnoses in approximately 30 min. It covers mood disorders (bipolar I & II, major depression, suicidality), anxiety disorders (social anxiety, panic, agoraphobia, generalized anxiety, PTSD, OCD), ADHD, eating disorders (anorexia, bulimia), substance use disorders (alcohol and other substances), and psychotic disorders. Its modular format allows rapid, reliable case‐finding in clinical trials and epidemiological studies. Test–retest reliability coefficients for major depression and anxiety diagnoses typically exceed *κ* = 0.70, and it shows good concordance with longer interviews such as The Structured Clinical Interview for DSM-5 [95]**Montgomery–Åsberg Depression Rating Scale (MADRS)** [78]: The MADRS is a clinician‐administered 10-item scale that quantifies depressive symptom severity over the preceding week. Each item (e.g., apparent sadness, inner tension, sleep, and appetite disturbances) is rated 0–6, yielding a total score from 0 to 60. The MADRS exhibits excellent inter‐rater reliability (ICC > 0.90) and sensitivity to treatment-induced change, making it a standard in antidepressant trials.**Quick Inventory of Depressive Symptomatology–Self-Report (QIDS-SR)** [70]: The QIDS-SR comprises 16 items mapping the nine core DSM-5 depressive domains (sad mood, anhedonia, concentration, self‐view, suicidal ideation, energy, sleep, appetite/weight, psychomotor changes) over the past 7 days. Responses use a 0–3 Likert scale, with composite scoring algorithms yielding a 0–27 total. Internal consistency is high (Cronbach’s *α* = 0.86–0.89), and the QIDS-SR correlates strongly with both the MADRS and HAM-D (*r* > 0.80), supporting its validity as a brief self‐report measure of depression severity.**Morningness–Eveningness Questionnaire (MEQ)** [86]: This 19-item self-report evaluates an individual’s circadian preference—“chronotype”—by asking about preferred timing for sleep, wakefulness, and peak performance. Scores classify respondents from “definite evening type” to “definite morning type.” The MEQ demonstrates good internal consistency (*α* ≈ 0.80) and has been validated against objective markers such as dim‐light melatonin onset.**Ultra-Short Munich Chronotype Questionnaire (μMCTQ)** [87]: The μMCTQ estimates chronotype via six items: usual sleep onset andsimi of work versus free days. By calculating the midpoint of sleep on free days corrected for accumulated sleep debt, it yields an estimate of intrinsic circadian phase. Test–retest reliability for sleep timing variables exceeds *r* = 0.90, and μMCTQ midpoints correlate well with full MCTQ scores.**Pittsburgh Sleep Quality Index (PSQI)** [84]: The PSQI is a 19-item self-report assessing sleep quality and disturbances over the past month across seven domains: subjective sleep quality, latency, duration, habitual efficiency, disturbances, medication use, and daytime dysfunction. Global scores > 5 indicate poor sleep. The PSQI’s internal consistency is acceptable (*α* = 0.75–0.83), and it discriminates insomniacs from healthy controls with a sensitivity of 89.6% and specificity of 86.5%.**Insomnia Severity Index (ISI)** [85]: The ISI consists of seven items rated 0–4 that probe the severity, impact, and perceived distress of insomnia symptoms. Total scores range from 0 to 28, with higher scores reflecting more severe insomnia. Internal consistency is excellent (*α* = 0.90), and the ISI correlates strongly with sleep diary metrics and polysomnographic indices, validating its use as a brief screening and outcome measure.**Consensus Sleep Diary(CSD)** [77]: A standardized daily log, the Consensus Sleep Diary captures subjective sleep–wake parameters—sleep onset latency, wake after sleep onset, total sleep time, time in bed, number and duration of awakenings, and morning sleep quality/refreshed ratings. It is the recommended unifying sleep diary for research, showing excellent agreement (*r* > 0.80) with actigraphy and flexibility for both EMA and weekly retrospective summary at follow‐up visits [77].**Short Form Health Survey (SF-12)** [82]: Derived from the SF-36, the SF-12 yields two summary scores—Physical Component Summary (PCS) and Mental Component Summary (MCS)—from 12 items covering domains such as physical functioning, role limitations, bodily pain, vitality, social functioning, and mental health. Despite its brevity, the SF-12 explains over 90% of the variance in SF-36 summary scores, exhibiting high test–retest reliability (ICC > 0.70) and construct validity across diverse populations.**Mental Health Quality of Life (MHQoL)** [83]: The MHQoL is a seven-dimension, four-level descriptive system (MHQoL-7D) plus a visual analogue scale (MHQoL-VAS, 0–10) for overall psychological well-being. Dimensions include self-image, independence, mood, relationships, daily activities, physical health, and outlook. It demonstrates good feasibility, content validity for mental health populations, and sensitivity to clinical change.**Credibility/Expectancy Questionnaire (CEQ)** [71]: The CEQ measures perceived treatment credibility and expectancy via six items: three assess credibility on a 1–9 scale and three assess expectancy on a 0–100% scale. Internal consistency ranges from *α* = 0.79 to 0.90, and early expectancy ratings predict clinical outcomes across psychotherapy and pharmacotherapy trials, underscoring its utility as a prognostic indicator.**Young Mania Rating Scale (YMRS)**: The YMRS is an 11-item clinician interview that quantifies manic symptoms—elevated mood, sleep, irritability, speech, thought content, motor activity, and insight. Items are weighted according to severity and duration (total score 0–60). Inter‐rater reliability is excellent (ICC > 0.85), and sensitivity to mood changes renders the YMRS a benchmark for bipolar disorder trials [74].**Adverse Event Scale for Light Therapy***:* A custom checklist will record the presence, frequency, and severity of known side effects of bright light exposure (e.g., headache, eyestrain, nausea), using Likert‐type ratings to facilitate systematic monitoring of tolerability throughout the intervention period.

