### Personal Illuminance Sensor

Participants wear a small, box-shaped light sensor developed by the Eindhoven University of Technology [88] near their clavicle from waking to bedtime during the baseline, treatment, and follow-up weeks to assess their light-related behaviors. This device uses a TAOSTCS34725 optical sensor and an onboard EEPROM memory of 64 kb. The sampling window is set to 30 s, meaning the device takes a light measurement every 10 s and averages these for the time window. To ensure optimal data collection, participants are instructed to turn the sensor upside down at bedtime to prevent it from measuring light exposure that does not actually fall on the eyes. Additionally, participants are advised to remove the sensor in wet conditions, as it is not water-resistant.

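### Objective (i) promises light-related behaviours as predictors of response, but none of the 21 predictors listed in the analysis section measures them

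*Protocol article*

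**What the plan says.** Under Objectives {7}, secondary objective (i) is the "identification of predictors of treatment response, encompassing baseline clinical characteristics, sleep metrics, circadian parameters, and light-related behaviors". The section on identification of predictors of response and remission restates the aim as finding "combinations of patient characteristics and behaviors that predict treatment response and remission". It then lists candidates under six labels: demographic, clinical, sleep-related, circadian, light-related and expectations. The clinical label holds "Clinical Diagnosis, Severity of Depressive Symptoms, Diurnal Variation in Affect". The light-related label holds a single item, Light Sensitivity. All predictors are to be measured at intake or in the baseline week. They go through stepwise logistic regression with bootstrap retention, in separate models for response and remission.

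The Light-related parameters section defines light sensitivity as the percentage fall in melatonin under light compared with dim light. The same section describes a set of exposure measures from the personal light sensor. The Personal Illuminance Sensor section says that participants wear the device in the baseline, treatment and "follow-up weeks to assess their light-related behaviors".

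**The concern.** The objective and the analysis that serves it disagree. Light behaviour is one of four predictor families promised by name, and a device is worn at baseline to measure it, yet the listed model has no place for it. The item under the light label measures how strongly melatonin responds to light. It does not measure how much light a person seeks or when.

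Two things are at stake. If the list is followed, objective (i) will be reported with one family untested. If the gap is noticed only at analysis, the light variable will be picked from many possible measures, inside a stepwise procedure, with the outcomes in hand.

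**Working it through.** The article states no figure on this point that could be reproduced. The check sets the objective beside the list and counts.

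**1. Count of listed candidates.** Demographic 3 + clinical 3 + sleep 8 + circadian 5 + light 1 + expectation 1 = 21.

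**2. Objective against list.**

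| Family promised in objective (i) | Candidates listed | Number |
|---|---|---|
| Clinical characteristics | diagnosis, severity, diurnal variation | 3 |
| Sleep metrics | the eight sleep-related items | 8 |
| Circadian parameters | the five circadian items | 5 |
| Light-related behaviours | none | 0 |
| Outside the four families | demographics 3, expectation 1, Light Sensitivity 1 | 5 |

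The total is 3 + 8 + 5 + 0 + 5 = 21.

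**3. Who has the one light entry.** Light sensitivity comes from the M2 saliva session, which belongs to the melatonin assessments (n = 72). The target enrolment is 231. 72 / 231 = 0.312, about 31%.

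**4. Who has the omitted measure.** The Baseline phase and Personal Illuminance Sensor sections describe the sensor for participants generally and state no subsample, whereas saliva, EMA and MRI each have one (72, 120 and 60). I take it from this that most participants should have baseline sensor data. The list therefore keeps the light variable that most participants will lack and omits the one that most should have.

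**5. How open the choice is if left until later.** The Light-related parameters section allows two light scales over five time windows: 2 × 5 = 10 level measures. It also names six thresholds (one at night, one in the morning, three in the day, one in the evening), each with a time-above and a timing measure: 6 × 2 = 12. That makes 10 + 12 = 22 possible variables, and the section calls them adjustable.

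**6. Room in the model.** If all 21 candidates enter one complete-case model, the melatonin items limit it to at most 72 people. Assume an outcome rate of 50%, which is the best case. Then at most 72 × 0.5 = 36 people fall in the smaller outcome group: 36 / 21 = 1.7 per candidate. With two variables added and none removed it is 36 / 23 = 1.6. Additions should therefore replace existing candidates.

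**7. Symptom features reviewed in the rationale.** Diurnal variation is listed. Hypersomnia is covered by proxy through sleep duration. Insomnia is covered through insomnia severity, onset latency and wake after sleep onset, and worse morning mood through diurnal variation. Appetite change, psychomotor retardation and guilt have no term. Coverage is partial.

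**The case against.** The list is introduced as what the predictors will include, the analysis plan is called an initial framework open to minor documented changes, and the light parameters are declared adjustable. The list also has a light-related label, so the family could be called thinly filled, and a condensed article may leave the choice of items to a fuller document. This stands against any reading that the list is closed. It does not remove the mismatch: the article prints both an objective and an itemised list, and nothing in the predictor section assigns the sensor measures to prediction.

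Sleep timing is also a behaviour, so the restated aim is arguably met without light. That is fair for the restatement, but objective (i) names light-related behaviours separately from sleep metrics.

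Sensor data do enter another analysis, the exploratory one on adherence under Methods for additional analyses. That concerns light received against the prescribed treatment schedule. It does not supply a baseline predictor.

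A reader might go further and infer that the trial cannot answer its own question about atypical and melancholic features, because the background says "Yet it remains unknown whether these results generalize across the full spectrum of unipolar and bipolar depressions". The documents do not support this. The sentence is rationale; it concerns symptom, chronotype and education findings, and it commits the trial to no particular test. Objective (i) asks only for clinical characteristics, which are listed, and the symptom features are partly covered.

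Nor can a useful power figure be attached to the omission. A calculation for one unadjusted predictor in the full sample would not describe a 21-candidate stepwise selection in which several variables exist only in subsets.

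**Conclusion.** The point holds for light behaviour. One of the four predictor families in objective (i) has no candidate among the 21 listed, and the only light entry is a physiological measure confined to about 31% of the target sample. This is a gap in prespecification: the baseline sensor data are being collected and the family can still be tested. It touches a secondary objective and leaves the primary comparison of the three arms unaffected. It should be corrected before outcomes are analysed.

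The conclusion assumes that the printed list is what will be run and that the sensor is not confined to a subsample, as the text suggests.

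The partial coverage of atypical and melancholic features is a lesser, optional matter. It is not a contradiction with any objective.

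**What to change.** Add to the predictor list one or two prespecified baseline-week light-exposure variables from the Light-related parameters section, for example log light level in the 3 h after waking and in the 3 h before bedtime. State the scale (illuminance or melanopic), the averaging rule and the minimum wear time. Remove the same number of overlapping sleep candidates so that the total stays at 21. If light behaviour is excluded deliberately, delete it from objective (i) instead.

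The cost is an edit to the analysis text and the loss of one or two overlapping sleep candidates. No new data or visits are needed, and with enrolment still open in the article's Trial status section, the change can be made before outcomes are analysed.

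Optionally, appetite, psychomotor and guilt-related features could be examined from baseline QIDS-SR items, since the instrument covers "energy, sleep, appetite/weight, psychomotor changes" as well as self-view. That would need a scoring rule fixed in advance, because the article describes only the total score, and it should also not enlarge the candidate set.
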